**Objective:**

The primary objective of this study was to evaluate the safety and tolerability of the TANCoV-1.3.20 nasal SARS-CoV-2 vaccine in healthy adult participants in Tanzania. The secondary objectives included the assessment of vaccine-induced humoral and cellular immune responses, and preliminary evaluation of dose-related immunogenicity.

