**Methods:**

TANCoV-1 is a phase 1/2a double-blinded, randomized controlled trial conducted in the Dar es Salaam and Mbeya regions of Tanzania. A total of 150 healthy participants were planned to be recruited and randomized at a 1:1:1 ratio to receive a TANCoV-1.3.20 vaccination dose of 100 µL with or without a booster, or 200 µL without a booster. Each dose group was planned to contain an intervention arm and a control arm in a 1:1 ratio. In general, 75 participants were planned to be assigned to the experimental arm, and another 75 participants were planned to be assigned to the standard arm. Participant recruitment was expected to take 6 months, with follow-up for 6 months post vaccination. The trial has two primary end points: (1) safety, as ascertained by the incidence of adverse events, and (2) immunogenicity, which involves local, humoral, and cellular immune responses. The trial enrolled healthy individuals aged between 18 and 45 years, who provided written informed consent and met all the inclusion criteria per the protocol. The data will be analyzed using Stata (version 14; StataCorp LLC). Findings will be reported according to the CONSORT (Consolidated Standards of Reporting Trials) guidelines.

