##### Secondary End Points: Immunogenicity End Points

The secondary end points are (1) the proportion of participants with a specific TANCoV-1.3.20 humoral response, (2) the magnitude of the specific cellular response to TANCoV-1.3.20, (3) the proportion of participants with serum-neutralizing antibody responses to TANCoV-1.3.20, and (4) the characteristics of the humoral response produced by the TANCoV-1.3.20 vaccine.

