### Sample Size Estimation

The sample size for this noninferiority clinical trial was calculated to compare the proportion of seroconversion on day 28 between participants receiving the investigational vaccine TANCoV-1.3.20 and those receiving the standard Sinopharm COVID-19 vaccine. On the basis of prior studies and seroconversion data from the Tanzanian setting, we assumed an 88% seroconversion rate for the control group (Sinopharm) and expected a 90% seroconversion rate in the experimental group. A noninferiority margin of 20 percentage points was set, meaning that TANCoV-1.3.20 would be considered noninferior if its seroconversion rate was not more than 20% lower than that of Sinopharm. Using a 1-sided significance level (α) of .05, 80% power (1−β), and a 1:1 allocation ratio (experimental: control), the required total sample size was estimated at 50 participants per group. The study includes 3 study groups, with 25 participants per arm, resulting in a total planned sample size of 150 participants. This sample size provides sufficient power to establish noninferiority if the lower bound of the CI for the difference in seroconversion remains above the preset margin. The calculation assumes binomial proportions and follows standard methods for noninferiority designs in parallel trials [30].

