#### Immunogenicity Assessment

The processed samples (sera) will be analyzed to evaluate immunoglobulin G (IgG) and immunoglobulin M (IgM) titers using the WANTAI SARS-CoV-2 Ab enzyme-linked immunosorbent assay. The resulting antibody concentrations will be quantified, and the values will be expressed as GMTs to provide a reliable summary measure of the immune response while minimizing the effect of extreme values or outliers.

In addition to humoral responses, the cell-mediated immune response will be characterized to provide insights into T-cell activation and cytokine production following vaccination. This will include an interferon-γ (IFN-γ) enzyme-linked immunospot assay to quantify antigen-specific T-cell responses, alongside an intracellular cytokine staining assay performed on cryopreserved PBMCs. The intracellular cytokine staining assay allows detailed profiling of cytokines such as IFN-γ, interleukin-2 (IL-2), tumor necrosis factor-α (TNF-α), and other relevant markers, enabling the evaluation of T-cell subsets (cluster of differentiation 4 [CD4^+^] and cluster of differentiation 8 [CD8^+^]) involved in vaccine-induced immunity.

All immunology work and long-term sample storage, for at least 15 years, will be centralized at the NIMR-Mbeya Center.

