#### Data Analysis

The data will be analyzed using Stata (version 14; StataCorp LLC). Findings will be reported according to the CONSORT (Consolidated Standards of Reporting Trials) guidelines. Primary analyses will be based on the intention-to-treat population, and secondary analyses will be based on the per-protocol population.

The primary end point will be analyzed via a marginal Poisson regression model fitted using generalized estimating equations, with the logarithm of follow-up time included as an offset and the study arm as the predictor. The incidence rate ratio and its 95% CI will be derived from the Poisson regression model. Incidence rates will also be calculated as the number of incident cases divided by the person-time in years, with person-time calculated from randomization to (1) the study end at 6 months after the last participant enrollment and (2) death or the time last seen if lost to follow-up. In addition, absolute effects on the primary endpoint will be summarized using risk differences (events per 1000 person-years) and their 95% CIs, estimated from the model-based predicted rates in each arm.

In a secondary analysis of the primary end point, we will adjust the Poisson regression model for covariates, defined a priori (age and sex). Each protocol analysis will be performed and defined according to reported adherence to the intended allocation. Subgroup analysis of the primary end point will also be performed via the Poisson model on the prespecified subgroup variables (age and sex).

Other secondary outcomes will be analyzed using generalized linear models, depending on their distributions. The mean difference with its 95% CI will be derived for a continuous outcome, and the odds ratio with its 95% CI will be estimated for a binary outcome.

AEs will be summarized according to the number and percentage of individuals experiencing AEs.

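### The noninferiority test on day-28 seroconversion that sizes the trial is not carried into the analysis sections, whose effect measures do not fit its 20-point margin

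*Protocol article*

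**What the plan says.** All references are to the protocol article.

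- **Sample Size Estimation** states: "The sample size for this noninferiority clinical trial was calculated to compare the proportion of seroconversion on day 28" between TANCoV-1.3.20 and Sinopharm. It assumes 88% for control and 90% for the experimental vaccine, 1-sided alpha .05, 80% power and 1:1 allocation. It adds: "A noninferiority margin of 20 percentage points was set". Noninferiority is to be claimed when the lower confidence bound for the difference lies above the margin. The result is 50 per group (25 per arm) and 150 over three groups.
- **Data Analysis** assigns the primary end point a marginal Poisson model with a follow-up-time offset and an incidence rate ratio. For other secondary outcomes, "the odds ratio with its 95% CI will be estimated for a binary outcome". The intention-to-treat set is primary and the per-protocol set secondary.
- **Statistical Analysis** gives Fisher exact tests for adverse events and two-sample tests for laboratory values.
- **Immunogenicity Analysis** defines a seroconversion rate against an antibody threshold. It then names paired t tests, signed-rank tests and one-way ANOVA as examples of how responses will be compared.
- **Secondary End Points: Immunogenicity End Points** lists, among others, "the proportion of participants with a specific TANCoV-1.3.20 humoral response". Day-28 seroconversion is not listed.
- **Immunogenicity Assessment** measures antibodies "using the WANTAI SARS-CoV-2 Ab enzyme-linked immunosorbent assay", the only serology assay it names.
- **Status.** Abstract, Methods: "The trial has two primary end points: (1) safety, as ascertained by the incidence of adverse events, and (2) immunogenicity". Abstract, Objective: "The secondary objectives included the assessment of vaccine-induced humoral and cellular immune responses".

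**The concern.** The seroconversion comparison is the only stated justification for the sample size, so a reader expects the analysis sections to perform it. They do not mention noninferiority, the margin or day 28. The methods they do give answer other questions: whether event rates differ, what the odds ratio is, or whether means differ.

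An analysis plan that followed Data Analysis faithfully would therefore report results with no noninferiority conclusion, on a scale that the margin does not fit. The unsettled status of immunogenicity adds to this, because it decides which method in Data Analysis applies. Recruitment is complete and statistical analyses are described as underway (Recruitment and Study Progress), so the sections should be aligned before results are known by arm.

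**Working it through.** **1. Reproduce the plan's sample size.** Inputs from Sample Size Estimation: control 0.88, experimental 0.90, margin 0.20, 1-sided .05 (z = 1.645), power 80% (z = 0.842).

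n per arm = (1.645 + 0.842)² × (0.90×0.10 + 0.88×0.12) / (0.20 + 0.02)² = (2.487)² × 0.1956 / 0.0484 = 24.99, so 25 per arm and 50 per group. This matches the plan. The sizing is not in dispute.

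**2. Look for the sized test in the analysis sections.**

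| If seroconversion is | Governing text | What it yields | Tests a difference against -20 points? |
|---|---|---|---|
| primary | Data Analysis, Poisson model | incidence rate ratio; risk difference per 1000 person-years | No |
| secondary and binary | Data Analysis, generalized linear model | odds ratio, 95% CI | No |
| covered by the immunogenicity text | Immunogenicity Analysis | paired t, signed-rank, ANOVA (examples) | No |

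The risk difference in the first row is a rate per person-time, not a difference in day-28 proportions. No route leads to the sized test.

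**3. Scale conflict.** Odds ratio when the experimental rate is exactly 20 points below control:

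- control 88%: (0.68/0.32) / (0.88/0.12) = 0.29
- control 95% (assumed): (0.75/0.25) / (0.95/0.05) = 0.16
- control 70% (assumed): (0.50/0.50) / (0.70/0.30) = 0.43

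No single odds-ratio limit stands for the 20-point margin.

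**4. Power of the sized test when it is written in.** At 25 v 25 the standard error is √(0.1956/25) = 0.0885, and 0.22/0.0885 = 2.487.

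- 1-sided .05 (2-sided 90% CI): Φ(2.487 − 1.645) = 80.0%. Exact enumeration: Wald 78.4%, Newcombe 77.4%, score 77.2%.
- 2-sided 95% CI: Φ(2.487 − 1.960) = 70.1%. Exact: Wald 70.0%, Newcombe 65.2%, score 59.8%. For 80% by formula, (1.960 + 0.842)² × 0.1956 / 0.0484 = 31.7, so 32 per arm.
- Three groups pooled, 75 v 75: standard error √(0.1956/75) = 0.0511, ratio 4.308. Power is 99.6% at 1-sided .05 and 99.1% with a 95% CI.

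These figures use the planned arm sizes. The article reports 169 enrolled but not the split by arm.

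**5. Endpoint and status.** The end-point list speaks of responses to TANCoV-1.3.20, which the article describes as derived from an avian coronavirus (The TANCoV-1.3.20 Vaccine). The named ELISA is for SARS-CoV-2. The list therefore does not identify the variable that was sized. Immunogenicity is primary in Abstract, Methods and in Anticipated Reporting, and Immunogenicity Analysis also calls its endpoints primary. It is secondary in Abstract, Objective and in the end-point section.

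**The case against.** The strongest reply is that Sample Size Estimation already fixes the endpoint, day, comparator, scale, margin, 1-sided alpha and lower-bound rule. A reader might infer from the analysis sections that the sized question cannot be answered or has no decision rule. That goes too far: the rule exists, and the margin was set in advance. Interval method and similar detail may also sit in an analysis plan that is not shown. This limits the point but does not remove it, because the analysis sections are not silent. They name methods, and those methods do not fit the rule.

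Other parts of the reply also stand:

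- **Power.** A reader might infer that the trial has only about 70% power. No section attaches a 95% CI to the seroconversion difference. The loss arises only if that level is applied to the rule within a 25 v 25 group, and it nearly vanishes if groups are pooled.
- **Odds ratio.** The sentence governs seroconversion only if seroconversion is secondary. If it is primary, the Poisson model applies, which fits no better. The tests in Immunogenicity Analysis are examples, not a closed list.
- **Antigen.** A reader might infer that the arms would be compared on an antigen given to only one of them. With one SARS-CoV-2 ELISA and one threshold described for all sera, a common assay is the natural reading. What remains is that the end-point list does not say so.

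**Conclusion.** The point holds as a failure to carry the sized test through. The analyses as written yield no noninferiority conclusion, their effect scale conflicts with the margin, the sized endpoint is not in the end-point list, and its status is contradictory. This is a conflict within the article and needs correcting because it concerns the only hypothesis for which the trial was sized.

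The sample size itself needs no change: 25 per arm gives 80% power by the plan's formula and about 77 to 78% by exact enumeration. That rests on the assumed 88% and 90%, 1-sided .05, and a test within each group, which the sizing implies but does not state. A fall to about 70% by formula (60 to 70% exact) is conditional on choosing a 95% CI for this difference at 25 v 25.

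**What to change.** 1. Name day-28 seroconversion, with the same assay and threshold in both arms, as the noninferiority endpoint. Add it to the end-point list and give it one status in the abstract, end-point, analysis and reporting sections.
2. In Data Analysis and Immunogenicity Analysis, analyse it as the risk difference, TANCoV-1.3.20 minus Sinopharm, with a named interval method. Conclude noninferiority if the lower limit of the 2-sided 90% CI, which matches the 1-sided .05, is above -20 points.
3. State whether the test is made within each group (25 v 25) or pooled (75 v 75).
4. Report the per-protocol result beside the intention-to-treat result. Whether both must succeed is for the sponsor to decide; the stated order of the two sets can stay.
5. State the power for the chosen method: at 25 v 25, 80% by formula and about 77 to 78% exact. If a 95% CI is preferred, restate it as about 70% by formula and 60 to 70% exact, depending on the interval.

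The cost is a wording change to the protocol and any analysis plan, dated before arm-level results are seen. It needs no new data, assay or participants.

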#### Statistical Considerations and Analysis

##### Statistical Analysis

An interim review of the data will be performed by the independent data and safety monitoring committee. This will be done when at least 80% of the participants have been followed for at least the first 3 months. This is beyond the halfway stage to ensure that the safety estimate calculated at this time is statistically stable. Early stopping is considered if the significance level is *P*=.001 or lower (ie, if the Haybittle-Peto boundary is used).

The final analysis will be conducted once all study participants have received all their vaccinations, completed the final visit, or permanently withdrawn from the study. Analyses will be based on the principles of intention-to-treat and per protocol.

Baseline characteristics will be summarized by study groups using appropriate summary statistics. The study participant characteristics to be summarized will include demographic variables and baseline values relevant to safety and immunogenicity. The number and percentage of participants experiencing any AEs or SAEs will be summarized by severity and their relationship with the study treatment for each group. The calculation of incidence rates of AEs will include each participant only once, either according to the worst severity or the first reported event. Rates of the various AEs will be compared between the study groups via the Fisher exact test and will be summarized via exact binomial CIs. Safety, hematological, and clinical chemistry laboratory parameters will be summarized at the study visit according to the study group. Comparisons will be performed using 2-sample *t* tests or nonparametric equivalents as appropriate for the data.

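### If each participant counts once for AE incidence, person-time should stop at the first event; as listed it does not, so the rates are too low as first-event rates and the rate ratio is in effect a risk ratio

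*Protocol article*

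**What the plan says.** The abstract makes AE incidence one of two primary end points: "safety, as ascertained by the incidence of adverse events". Three parts of the Methods bear on how it is calculated.

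- **Numerator.** Statistical Analysis: "The calculation of incidence rates of AEs will include each participant only once". The event that counts is the most severe one or the earliest one.
- **Denominator.** Data Analysis: "Incidence rates will also be calculated as the number of incident cases divided by the person-time in years". Person-time starts at randomization and runs to "the study end at 6 months after the last participant enrollment and (2) death or the time last seen if lost to follow-up".
- **Model.** Data Analysis specifies a marginal Poisson regression (a GEE fit), "with the logarithm of follow-up time included as an offset and the study arm as the predictor". The model yields a rate ratio between arms with a 95% interval. Absolute effects come from the same model. They are called risk differences but are expressed per 1000 person-years.

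Two other statements matter for the reading. The safety end points section defines all three end points as proportions of participants: solicited AEs on days 1 to 7, unsolicited AEs of grade 2 or higher through day 28, and SAEs throughout the study. Statistical Analysis compares AE rates with the Fisher exact test and summarizes them with exact binomial CIs.

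**The concern.** In a first-event rate, a participant is at risk only until that event. Under the once-only rule, someone with an AE on day 2 can add no further event, yet by the listed stopping points still adds months of person-time. The denominator then includes time in which no event could be counted. The surplus grows with the share of participants who have an event, so the rate is understated more in the arm with more events.

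What is at stake is the meaning of the headline safety results. A reader given an incidence rate ratio and a difference per 1000 person-years will take them as rate measures. Under a once-only count over full follow-up they are risks divided by a follow-up time. The problem does not depend on how long follow-up or the AE windows are. It arises whenever a once-only count is divided by time that continues after the event.

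**Working it through.** The article states no AE risk, rate or rate ratio, so there is no figure of its own to reproduce.

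**Inputs.** Follow-up T = 0.5 year (6 months post vaccination, abstract). The AE risk p over that period is an assumption and is varied below.

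**Rate as written.** Once-only count over full follow-up: p / T. The ratio of two arms is (p₁/T) / (p₀/T) = p₁/p₀. T cancels, and what remains is the risk ratio.

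**First-event rate, time stopped at the event.** Under a constant hazard λ, p = 1 − exp(−λT). Mean time at risk is p/λ, so events over time at risk is λ = −ln(1 − p) / T.

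**Worked case, 30% v 60%.**
- As written: 0.30/0.5 = 0.600 and 0.60/0.5 = 1.200 per person-year, or 600 and 1200 per 1000. Ratio 2.00, difference 600.
- Stopped: −ln(0.70)/0.5 = 0.713 and −ln(0.40)/0.5 = 1.833, or 713 and 1833 per 1000. Ratio 2.57, difference about 1120.
- Understatement: 1 − 600/713 = 15.9% and 1 − 1200/1833 = 34.5%.

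**Range, constant hazard, T = 0.5 year.**

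| Assumed AE risks | As written, per 1000 | Stopped, per 1000 | Too low by | Ratio as written | Ratio stopped |
|---|---|---|---|---|---|
| 2% v 4% | 40 v 80 | 40 v 82 | 1.0%, 2.0% | 2.00 | 2.02 |
| 10% v 20% | 200 v 400 | 211 v 446 | 5.1%, 10.4% | 2.00 | 2.12 |
| 30% v 50% | 600 v 1000 | 713 v 1386 | 15.9%, 27.9% | 1.67 | 1.94 |
| 30% v 60% | 600 v 1200 | 713 v 1833 | 15.9%, 34.5% | 2.00 | 2.57 |

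**Common study end.** The listed study end is 6 months after the last enrollment. With enrollment uniform over the planned 6 months and the same hazards as in the 30% v 60% case, a simulation of 2,000,000 per arm gives a ratio of 1.79 as written and 2.57 stopped.

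**Sensitivity to event timing.** If all events fall at time t, the stopped rate is p / [(1 − p)T + p·t].
- *Events at day 3, 6-month denominator, 30% v 60%:* 0.30/(0.35 + 0.30 × 3/365.25) = 0.851 and 0.60/(0.20 + 0.60 × 3/365.25) = 2.928 per person-year. Ratio 3.44.
- *Same events, time at risk limited to a 7-day window:* 0.30/(0.70 × 7 + 0.30 × 3) = 0.30/5.8 and 0.60/(0.40 × 7 + 0.60 × 3) = 0.60/4.6 per day. Ratio 2.52. Much of the gap between 2.00 and 3.44 therefore comes from the long denominator.
- *Different timing, 30% at day 3 v 40% at day 170, 6-month denominator:* ratio 1.33 as written and 0.97 stopped. The as-written ratio is not always the one nearer 1.

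**The case against.** **The once-only rule may belong to a different analysis.** It sits among numbers and percentages of participants, offers worst severity as an alternative (a tabulation rule with no person-time meaning), and is followed by Fisher tests and binomial CIs. In that section, incidence rates can well mean proportions, for which counting once is correct. This stands for those summaries. It does not settle Data Analysis, whose own rate divides incident cases by person-time that continues after the event.

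**Data Analysis may intend all events to be counted.** It speaks of events per 1000 person-years, and with all events counted, full follow-up is the right denominator. The reading is possible, but incident cases points the other way and nothing in the article says that repeat events count. The mismatch is therefore conditional on a once-only count.

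**A reader might infer that the plan shrinks or conceals a real excess of harm.** The article does not support that. Its safety end points are proportions, and with similar follow-up in the arms the as-written ratio is the relative risk for such proportions: 60% v 30% gives 2.00, which is correct as a risk ratio. The first-event rate ratio is a different quantity, not the truth from which 2.00 departs. The direction also depends on timing, and the participant percentages, Fisher tests and exact CIs are unaffected.

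**A condensed article leaves detail to the full protocol or SAP.** True in general, but here the stopping points and the offset are stated explicitly.

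**Conclusion.** The point holds on condition that the count is once-only. As first-event measures, the rates and the difference per 1000 person-years are then too low, by more in the arm with more events when timing is similar. Under the assumed 30% v 60% risks and constant hazard over 6 months, the shortfall is 16% and 35%. At 2% v 4%, a level plausible for SAEs, it is 1% to 2% and the ratio barely moves (2.00 against 2.02). All sizes rest on assumed risks and timing.

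The ratio is in effect a risk ratio under the wrong name. With similar event timing in the arms it lies nearer 1 than the first-event rate ratio, but it remains a valid relative risk for the stated end points. The defect is one of matching numerator, denominator and label in the primary safety model; it is not evidence that harm would go unseen. The correction is worth making because AE incidence is a primary end point and the change costs little.

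**What to change.** Amend Data Analysis to adopt one of the following, and state whether each participant counts once or for every event.

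- **(a) First-event rate.** For once-only counts, end both person-time and the Poisson offset at the earliest of first qualifying event, end of that outcome's observation window, death or last contact.
- **(b) Event rate.** Keep full follow-up as denominator and offset, and count all events per participant.
- **(c) Risk.** Analyse the stated proportions as risks, with a risk ratio and risk difference and no person-time offset, and label them so. This lies closest to the end points as defined.

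The Fisher tests and exact binomial CIs on participants with an AE can stay; a few words saying that incidence rate there means the proportion of participants would remove the ambiguity.

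The cost is analysis wording and, for (a), an offset recalculated from AE onset dates, which the diary cards, AE form and planned evaluation of AE duration imply are recorded. No new data are needed. The article says outcomes will be analysed after follow-up and assays are complete, so the choice should be recorded before comparative safety results are seen.

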### Randomization

Eligible participants will be randomized to the intervention arm or control arm via permuted block randomization with a block size of 6 stratified by site. This method ensures a balanced allocation of participants among the groups. Participants fulfilling the eligibility criteria will be randomized sequentially, and each participant will have a unique randomization code. A randomization schedule will be created by an independent statistician via permuted-block randomization of variable size.

Before enrollment, the study screening electronic case report form must be completed. When a participant is confirmed to be eligible and has consented to be enrolled, their details will be entered on the next available line of the enrollment register to ascertain the trial number assigned to that participant, which will be used on all trial documents. This number is unique and will not be used for any other participant.

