##### Immunogenicity Analysis

The primary endpoints of the immunogenicity analysis will focus on quantifying and comparing immune responses elicited by the vaccine across study groups and time points. The seroconversion rate will be determined as the proportion of participants who achieved a predefined antibody threshold postvaccination relative to their baseline levels, indicating the vaccine’s ability to induce a measurable immune response. In addition, GMTs for antibody concentrations or the mean fluorescence intensity for flow cytometry–based assays will be calculated to summarize central tendencies of immune responses while minimizing the influence of extreme values. These parameters will be statistically compared across treatment arms, dose groups, and time points via appropriate statistical tests such as paired 2-tailed *t* tests, Wilcoxon signed-rank tests, or one-way ANOVA, depending on the data distribution. Additionally, to assess immune kinetics, longitudinal models, which describe patterns of immune waning or boosting following primary and subsequent vaccine doses, will be used. Furthermore, correlation analyses, including protection against infection during the entire study period, will be performed to explore the relationship between antibody levels and clinical outcomes, thereby identifying potential immunological correlates of protection and revealing the predictive value of measured immune parameters.

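### Laboratory safety values are compared by 2-sample t tests that cannot use the baseline value or site; regression on arm, baseline and site would be more precise at almost no cost

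*Protocol article*

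**What the plan says.** **Laboratory safety data.** Under Statistical Considerations and Analysis, subsection Statistical Analysis, the article says that "clinical chemistry laboratory parameters will be summarized at the study visit according to the study group". It then adds: "Comparisons will be performed using 2-sample" t tests or nonparametric equivalents. The same subsection lists "demographic variables and baseline values relevant to safety and immunogenicity" among the characteristics to be described by group. Baseline is given no other role in the laboratory analysis.

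**Randomization and site.** Randomization is by "permuted block randomization with a block size of 6 stratified by site". Study Sites sends the Dar es Salaam safety samples to one laboratory and the Mbeya safety samples to another. All immunogenicity samples go to a single laboratory. Site appears in no analysis named in the article.

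**Immune responses.** Immunogenicity Analysis says: "These parameters will be statistically compared across treatment arms, dose groups, and time points". The tests offered as examples include paired t tests, "Wilcoxon signed-rank tests, or one-way ANOVA, depending on the data distribution". The section also plans longitudinal models and defines seroconversion as "the proportion of participants who achieved a predefined antibody threshold postvaccination relative to their baseline levels".

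**Models elsewhere.** Data Analysis assigns other secondary outcomes to generalized linear models, with a mean difference for continuous outcomes, and names no covariates for them. The only stated adjustment is for age and sex in the Poisson model of the primary end point.

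**The concern.** A laboratory value measured before vaccination may predict the same participant's later value. If it does, a 2-sample t test of the later value leaves removable variation in the error term. With 25 participants per arm this can matter: the difference in baseline means between two arms has a standard error of sqrt(2/25) = 0.28 SD by chance alone.

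Site is a second source. Any systematic difference between the two safety laboratories goes into the t-test residual. Leaving out a factor used to stratify randomization also tends to make the standard error too large.

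At stake is how readily a shift in a safety laboratory mean, or a difference between dose groups, can be seen. The formal safety end points are not at stake. They are proportions of participants with adverse events, and laboratory results enter them only as graded events.

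**Working it through.** **1. The plan's own sample size.** Sample Size Estimation gives 88% and 90% seroconversion, a margin of 20 percentage points, one-sided alpha 0.05 and 80% power.

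- n per arm = (1.645 + 0.842)² × (0.88×0.12 + 0.90×0.10) / (0.20 + 0.02)² = 6.183 × 0.1956 / 0.0484 = 24.99, so 25.
- This gives 50 per group and 150 in total, with power 80.0%. The stated size reproduces when the 50 is read as two arms of 25.
- It rests on a binary end point, so the present point does not alter it.

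**2. Inputs for the laboratory comparison.**

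- n = 25 per arm (Sample Size Estimation; Table 1).
- Correlation r between baseline and follow-up: not given. Assumed, range 0 to 0.7.
- Difference of 0.5 SD for the power illustration, two-sided 5% level: also assumed.

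**3. Formulas.** Relative to an unadjusted t test of the visit value, adjustment for baseline multiplies the variance of the arm difference by (1 − r²) × [1 + 1/(2n − 4)]. The second factor, 1 + 1/46 = 1.022, is the price of estimating the slope. The equivalent unadjusted n per arm is 25 divided by this ratio. Power is from the noncentral t distribution, with 48 degrees of freedom unadjusted and 47 adjusted.

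**4. Results.**

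| Assumed r | Variance ratio | Equivalent n per arm | Power for 0.5 SD |
|---|---|---|---|
| unadjusted | 1.00 | 25 | 41% |
| 0 | 1.02 | 24.5 | 40% |
| 0.3 | 0.93 | 26.9 | 44% |
| 0.5 | 0.77 | 32.6 | 51% |
| 0.6 | 0.65 | 38.2 | 57% |
| 0.7 | 0.52 | 48.0 | 67% |

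Ignoring the slope-estimation factor, the difference detectable with 80% power is 0.81 SD unadjusted, 0.70 SD at r = 0.5 and 0.58 SD at r = 0.7.

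**5. If the t test is applied to the change from baseline.** The article does not say whether the visit value or the change is tested. The variance of a change, relative to the visit value, is 2(1 − r): 1.4 at r = 0.3, 1.0 at 0.5 and 0.6 at 0.7. Regression on baseline has a lower variance than the change at each of these: 0.93 against 1.4, 0.77 against 1.0, and 0.52 against 0.6.

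**6. Site.** Assume two sites of equal size whose means differ by d within-site SDs. The share of total variance due to site is (d²/4)/(1 + d²/4). For d = 0.5 this is 0.0625/1.0625 = 6%; for d = 1 it is 0.25/1.25 = 20%. The article gives no value of d.

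**The case against.** **The tests are valid.** Randomized arms compared without adjustment give an unbiased estimate, and chance imbalance is already reflected in the standard error. The laboratory means by visit are supportive and are not a listed end point. All of this stands, and it limits the point to precision.

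**The gain is assumed.** The article gives no correlation. At 0.3 or below the gain is slight, and at 0 it is slightly negative. Enrollment reached 169, about 28 per arm if split evenly over six arms, so 25 is a little pessimistic. This also stands, and the result is therefore given as a range.

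**Covariates may be left to an analysis plan that is not shown.** This stands for the generalized linear models, whose terms are open. It does not stand for the laboratory data, where the article names a method that has no place for a covariate.

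**Readings that go too far.** Three are tempting:

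- *That the immune analyses ignore baseline.* They do not. Seroconversion is defined relative to baseline, paired tests and longitudinal models are planned, and the list of tests is illustrative. Only a one-way ANOVA across arms, if used, would lack a baseline term.
- *That the authors considered and rejected baseline adjustment because participants enter antibody-negative.* The article never discusses the matter. The negative test is an eligibility criterion and nothing more.
- *That the laboratory tests are certainly of raw post-vaccination values.* The text does not settle this. As step 5 shows, regression is the more precise choice either way.

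**Conclusion.** The point holds as a free improvement of low severity. It is firm for hematology and chemistry: the named test cannot use baseline values that are collected, or the site factor by which randomization was stratified and by which the safety laboratories differ. If the correlation with baseline is 0.5 to 0.7, the variance falls by about 23% to 48%, worth about 8 to 23 extra participants per arm. If it is 0.3 or less, little is gained. The correlation and the site difference are assumptions, not figures from the article.

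For immune responses the point is narrower. It concerns continuous comparisons between arms, such as the magnitude of the cellular response. It does not concern the secondary end points that are proportions. For SARS-CoV-2 antibody, entry requires a negative test, so baseline should vary little and adjusting for it would bring almost nothing. Neither the sample size nor any primary conclusion is affected.

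**What to change.** 1. **Laboratory values.** Replace the 2-sample t test with linear regression of the visit value on arm, baseline value and site. Use a transformation or a rank-based version where values are skewed. Keep the by-visit tables for description.
2. **Continuous immune comparisons between arms.** Use the linear model that Data Analysis already allows, on the log scale, with arm and site and, where baseline varies, the baseline value.
3. **SARS-CoV-2 antibody.** Adjust for site only.

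The cost is a change of wording and one or two degrees of freedom; no new data are needed. Because the article reports data cleaning and statistical analyses as underway, the terms should be fixed in writing before any comparison by arm is seen.
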